### Study population and sample size

The study population will be selected among patients from the Ischemic Heart Disease outpatient clinic at HCPA, a tertiary care university hospital in South Brazil. All clinic patients have CAD defined by the presence of at least one of the following: documented history of myocardial infarction, surgical or percutaneous myocardial revascularization, lesion > 50 % in at least one coronary artery assessed by angiography, or presence of angina and positive noninvasive testing of ischemia [8].

Study participants will undergo standard anamnesis and medical examination to verify clinical stability and discharge criteria.

The sample size was calculated as 140 patients in each group—considering a non-inferiority margin of 10 % and incidence of 92 % of the main outcome, that is, maintenance of Canadian Cardiovascular Society Functional Classification (CCS) 12 months after the start of follow-up. This was based on the rate of patients with increase in angina to a higher CCS reported by a previous study for the control group receiving optimal treatment for CAD [9]. An additional 10 % margin was added to account for losses to follow-up. For calculation of sample size, a ß of 0.9 and an α of 0.05 (two-sided) were considered.

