### Randomization

Patients eligible for inclusion will be randomized 1:1 using random block sizes of six and four, by a computerized list provided by randomization.com. The investigator in charge of randomization will not be involved in determination of eligibility or assessment of outcomes. Group assignment will be performed by opening a sealed opaque envelope in front of the patient after signature of the informed consent form and completion of the initial research questionnaire. After that, the groups will be managed as follows (Fig. 1):Telehealth group (intervention group): the patient will be discharged from the tertiary care outpatient clinic and directed to a primary care facility (Basic Health/Family Health Strategy unit) previously identified according to residential address. At the primary care facility, patients will book a routine appointment within two months. For that, the patient will bring the discharge note, comprising all relevant information about the case, medical prescriptions, and a counter-reference note with therapeutic planning. The TelessaúdeRS/UFRGS team will contact the basic health unit and provide access to the telehealth platform for follow-up monitoring. A teleadvisory will be scheduled between the medical teleconsultants and the primary physicians within two months after outpatient clinic discharge to discuss clinical management of the patient. Furthermore, primary physicians can call the support team at TelessaúdeRS/UFRGS whenever they have doubts about the clinical management. Patients will be interviewed by telephone at four and eight months of follow-up using the standardized instrument used at study entry. The calls will be made by independent evaluators, hired and trained specifically for this purpose. An appointment will be booked at 12 months of follow-up for final evaluation of the patient.Control group: patients will undergo the usual flow routine during the study period. Patients will be interviewed by telephone using the standardized instrument at four and eight months of follow-up. An appointment will be booked at 12 months of follow-up for final evaluation of the patient. Ifclinical status is stable, the patient will no longer attend the tertiary outpatient clinic for follow-up.

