### Outcome measures and assessment procedures

Telephone interviews aim to identify changes in functional class or clinical events taking place over the follow-up period.

The final 12-month interview will evaluate the same components assessed in the initial interview, in order to determine improvement/worsening of clinical status. All patients will undergo blood tests with serum lipids and glucose evaluation.

The primary outcome is maintenance of CCS I or II at 12 months.

Secondary outcomes focus on risk factors. Control of risk factors will analyze variations of at least 5 % in the following pre and post-intervention measurements [12]:systemic blood pressure;controlled dyslipidemia: LDL < 100 mg/dL;glycated hemoglobin (in the presence of diabetes);abstinence from tobacco smoking;about 150 min/week of regular physical activity.

Additional secondary outcomes include health care access variables, such as: medical appointment in primary care facility taking place within not more than six months after referral, with review of medications and issue of prescriptions; and disease instability during the 12-month follow-up, defined as the need for seeking emergence care due to cardiovascular disease: acute chest pain; heart failure decompensation; acute arrhythmias; stroke.

Given the objective nature of the outcomes, the safety of the intervention, and the brief follow-up period, endpoint adjudication and data monitoring committees will not be appointed. No interim analyses are proposed. At the 4 and 8-month telephone interviews patients will be asked about possible unintended effects of the trial, and will receive guidance as required. After the trial, patients will be readmitted to the outpatient clinic if continued care at a primary care facility is not available.

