### Statistical analysis

Continuous variables without normal distribution will be described as mean ± standard deviation or median and inter-quartile range (IQR). Categorical variables will be expressed as percentages. Comparisons between groups will be performed by Student’s *t*-test for continuous variables with normal distribution and Wilcoxon’s test for variables without normal distribution. Fisher’s exact test will be used for categorical variables. Logistic regression analysis will be used to establish the effect of the counter-referral strategy on primary and secondary outcomes at 12 months. Analysis of survival free of events at 12 months will be performed using the Cox multivariate regression and described in Kaplan-Meier survival curves. Variables with *P <* 0.10 in the univariate analyses will be included in the multivariate model. Primary outcome analysis will be according to intention to treat (ITT). Determination of sample size has taken into consideration a 10 % loss to follow-up.

Data will be analyzed in SPSS 18.0 for Windows. Statistical significance is set at *P <* 0.05.

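### The continuous risk-factor outcomes are compared unadjusted or as yes/no, and the baseline value is not pre-specified as a covariate

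*Protocol article*

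**What the plan says.** Under Outcome measures and assessment procedures, the protocol article lists blood pressure, LDL (with a target below 100 mg/dL) and HbA1c (where diabetes is present) among the secondary outcomes. Control is judged by a change of 5% or more "in the following pre and post-intervention measurements". The 12-month assessment repeats what was recorded at entry, so each of these measures is meant to have a baseline and a follow-up value.

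The Statistical analysis section then assigns the methods:

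- Student's t-test "for continuous variables with normal distribution", and Wilcoxon's test otherwise.
- Fisher's exact test for categorical variables.
- For the treatment effect: "Logistic regression analysis will be used to establish the effect of the counter-referral strategy on primary and secondary outcomes at 12 months".
- A multivariate model that takes in variables with univariate P < 0.10.

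No linear model with the baseline value as a covariate is named. No effect size, SD, correlation or power is stated for the risk-factor outcomes.

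**The concern.** A two-sample test on the 12-month value leaves the baseline reading unused. A logistic model needs the measurement cut into yes/no first, which discards most of the information about how far it moved. Neither is the efficient way to compare a continuous measure that each patient provides twice.

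The abstract and the Discussion say that these stable patients mainly need risk-factor monitoring and prescription review. The risk-factor outcomes are therefore where a decline in care after discharge would be expected to show. The Discussion expects follow-up quality to be similar in the two settings. No non-inferiority margin is given for these outcomes, so the precision of the estimated difference is the reader's main guide to how much worsening can be excluded. An imprecise comparison is easier to misread as similarity.

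**Working it through.** **The plan's own figure.** The only sample-size figure concerns the primary outcome: "The sample size was calculated as 140 patients in each group", "considering a non-inferiority margin of 10 % and incidence of 92 % of the main outcome", with "a ß of 0.9 and an α of 0.05 (two-sided) were considered" (the 0.9 being evidently power).

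- One-sided α 0.05: (1.645 + 1.282)² × 2 × 0.92 × 0.08 / 0.10² = 126.06, so 127. Multiplying 126.06 or 127 by 1.1 and rounding gives 139 to 140, which matches 140.
- Two-sided 0.05 read literally: 155, then 171 after the same inflation, which does not match.

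That mismatch is a separate matter. What is needed here is the number evaluable. The plan allows for loss ("An additional 10 % margin was added to account for losses to follow-up"), so 140 × 0.9 = 126 per arm.

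**Assumptions, none of them in the document.** Systolic pressure with mean 135 mmHg and SD σ = 18 mmHg at both times; true difference δ = 5 mmHg; baseline-to-12-month correlation r = 0.3, 0.5 or 0.7; two-sided 0.05; n = 126 per arm.

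**Continuous analyses.** Power = Φ(δ / (s√(2/n)) − 1.96), with √(2/126) = 0.1260 and

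- 12-month value: s = σ = 18
- change: s = σ√(2(1 − r))
- ANCOVA: s = σ√(1 − r²)

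At r = 0.5, the 12-month value gives 5 / (18 × 0.1260) = 2.205 and Φ(0.245) = 0.597. ANCOVA has s = 15.59, giving 5 / 1.964 = 2.546 and Φ(0.586) = 0.721.

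**Yes/no analysis.** The proportions with a rise of 5% or more were simulated under the same assumptions: 0.379 v 0.468 at r = 0.3, 0.357 v 0.463 at r = 0.5, and 0.319 v 0.452 at r = 0.7. With p̄ the mean of the two, power = Φ{(|p₁ − p₀| − 1.96√(2p̄(1 − p̄)/n)) / √([p₀(1 − p₀) + p₁(1 − p₁)]/n)}. At r = 0.7 this is Φ((0.133 − 0.120)/0.0607), about 0.58. This large-sample test is close to an unadjusted logistic regression. Fisher's exact test is lower.

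| Analysis | r = 0.3 | r = 0.5 | r = 0.7 |
|---|---|---|---|
| t-test, 12-month value | 60% | 60% | 60% |
| t-test, change | 46% | 60% | 81% |
| 5% rise, large-sample test | 30% | 40% | 58% |
| 5% rise, Fisher | 25% | 35% | 53% |
| ANCOVA on baseline | 64% | 72% | 87% |

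**Gain from ANCOVA, in percentage points, from the unrounded values.**

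- Over the 12-month t-test: 63.7 − 59.7 = 4.0; 72.1 − 59.7 = 12.4; 87.0 − 59.7 = 27.3.
- Over the change t-test: 63.7 − 46.2 = 17.5; 72.1 − 59.7 = 12.4; 87.0 − 81.2 = 5.8.
- Over the 5% rise by the large-sample test: 63.7 − 30.0 = 33.7; 72.1 − 39.9 = 32.2; 87.0 − 58.4 = 28.6.

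ANCOVA is ahead in every column. Its lead over a t-test depends strongly on r; its lead over the yes/no version is large throughout.

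**The case against.** The strongest reply is that the plan does use baseline. The 5% criterion is built from the pre and post values, a t-test could be run on change, and the P < 0.10 rule could bring the baseline value into a multivariate model. This stands. A reader might infer that the baseline values are ignored, and the document does not support that. What is missing is narrower: baseline is not fixed in advance as a covariate. A data-driven rule does not fix it, and the model named for the effect is still logistic.

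Second, a reader might infer that much of the power is lost whichever test is used. That does not hold either. The gain over a t-test can be as small as 4 points (12-month value, r = 0.3) or 6 points (change, r = 0.7). The heavy loss comes from the yes/no definition and not from omitting the covariate alone. LDL below 100 mg/dL is a legitimate target-level outcome, and logistic regression suits it. The continuous analysis should therefore be added and should not abolish the stated control measures.

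Third, the data may be thinner than 126 per arm. HbA1c applies only to patients with diabetes, and the 12-month blood tests described are lipids and glucose. Baseline information may come from records, and patients who miss the final visit are contacted by telephone, which yields no new blood test. This stands too, and limits the analysis to patients with both measurements.

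Finally, unadjusted tests in a randomised trial are valid, and a full analysis plan may exist. But the article does not leave the method open: it names the tests and the effect model for the secondary outcomes. The point is about that stated choice and not about an omission.

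**Conclusion.** The point holds as one of efficiency for secondary outcomes. The stated methods are unadjusted comparisons or yes/no analyses, and baseline is not pre-specified as a covariate although it is to be measured. In the systolic pressure example, ANCOVA improves on a t-test by roughly 4 to 27 points of power, depending on the correlation and on whether the 12-month value or the change is tested. It improves on the 5% yes/no version by about 29 to 34 points under the large-sample test, and by somewhat more under Fisher.

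These sizes rest on an assumed SD, difference and correlation. Only systolic pressure was modelled, so LDL and HbA1c will differ in degree. No figure in the document is shown to be wrong, and the binary primary outcome and its sample size are untouched. Nor does the document say that a non-significant secondary test will be taken as proof of similarity; that is a risk in interpretation, which a more precise estimate with its interval reduces but does not remove.

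**What to change.** In the Statistical analysis section, add that the 12-month values of blood pressure, LDL and HbA1c (the last in patients with diabetes) will each be analysed, among patients with both measurements, by a linear model on arm and the patient's own baseline value. The adjusted mean difference should be reported with its 95% CI. Keep the 5% change and LDL < 100 mg/dL measures as stated outcomes, reported alongside.

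The cost is one sentence and one added analysis per risk factor. It uses measurements the protocol already lists and is a standard covariance model in the software named. The state of HbA1c collection at 12 months should be confirmed when the sentence is written.

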### Interview and questionnaires

Eligible individuals will be invited at the outpatient clinic, after their regular appointment, to participate in the study. At study entry, patients will undergo a baseline interview (Fig. 1). Interviews will be performed by a trained professional using a standard pre-coded questionnaire. The following information will be collected by interview or review of medical records: (i) clinical and epidemiological data: previous diagnoses, including chronic heart failure, peripheral arterial disease, acute myocardial infarction (AMI), chronic arterial disease, chronic obstructive pulmonary disease (COPD), dyslipidemia and diabetes; Canadian Cardiovascular Society (CCS) Functional Classification of Angina grade at the moment of the interview [10]. (ii) Biological factors: age and sex. (iii) Socioeconomic factors: skin color, social class, literacy, income, and schooling. (iv) Lifestyle: alcohol consumption, smoking, and practice of physical activities. (v) Use of medications: dose and type of medications, adherence to drug treatment (measured by an adapted version of the Brief Medication Questionnaire). (vi) Laboratory tests and medical procedures performed.

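### Covariates for the multivariate model are chosen by univariate P < 0.10, so the adjusted odds or hazard ratio is defined by the outcome data and baseline CCS class has no assured place

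*Protocol article*

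**What the plan says.** All analysis text is in the protocol article, section Statistical analysis. Three sentences bear on this point.

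- Binary outcomes: "Logistic regression analysis will be used to establish the effect of the counter-referral strategy on primary and secondary outcomes at 12 months".
- Time to event: "Analysis of survival free of events at 12 months will be performed using the Cox multivariate regression".
- Covariates, directly after the Cox sentence: variables enter if their P-value is below "0.10 in the univariate analyses will be included in the multivariate model".

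This is the only covariate rule in the document. It names no covariates, sets no limit relative to the number of events, does not mention the arm, and refers to a single multivariate model without saying which one.

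The pool that could be screened is the baseline list in Interview and questionnaires. That list includes the CCS "Functional Classification of Angina grade at the moment of the interview", the baseline value of the scale on which the primary outcome is defined.

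**The concern.** Randomisation already protects the comparison from systematic confounding. Adjustment here serves to account for known prognostic factors, so the factors should be chosen on prior grounds. A P-value screen chooses them from the same outcome data that are then used to estimate the treatment effect.

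Three things follow.

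- Odds ratios and hazard ratios are non-collapsible: their value changes with the covariates conditioned on, even without confounding. If the covariate set is settled by the data, so is the quantity being estimated.
- With few failures and many candidates, some of the variables that enter will be noise.
- Baseline CCS class may be left out by chance. Eligible patients are in class I or II and success is staying in class I or II, so a class II patient is one step from failure and a class I patient is two. That makes it a natural adjustment variable, though the documents give no figure for its prognostic strength.

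**Working it through.** **Inputs.** From Study population and sample size: "The sample size was calculated as 140 patients in each group"; "non-inferiority margin of 10 % and incidence of 92 % of the main outcome"; "a ß of 0.9 and an α of 0.05 (two-sided) were considered"; "An additional 10 % margin was added to account for losses to follow-up". The 0.9 is read as 90 % power. From Statistical analysis: entry threshold 0.10. From Interview and questionnaires, my count of candidates: 7 diagnoses + CCS grade + age and sex (2) + 5 socioeconomic items + 3 lifestyle items + medication and adherence (2) = 20, before laboratory tests and procedures. The document does not call these model candidates, so 20 is an assumption and a range of 10 to 25 is shown.

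**The plan's own figure.** n per group = (z_α + z_β)² × 2 × 0.92 × 0.08 / 0.10².
- One-sided α 0.05: (1.645 + 1.282)² × 14.72 ≈ 126.1, so 127; × 1.1 = 139.7, so 140. This reproduces the stated size.
- Two-sided 0.05 as written (one-sided 0.025): 155, then 171 (× 1.1) or 173 (÷ 0.9). This does not reproduce it. That is a separate matter; the event counts below need only 280, 8 % and 10 %.

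**Failures on the primary outcome.**
- No loss: 280 × 0.08 = 22.4.
- After 10 % loss: 280 × 0.9 = 252; 252 × 0.08 = 20.2 (95 % binomial range 12 to 29).

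**Noise variables passing P < 0.10.** With k unrelated, independent candidates, the expected number is 0.10k and the chance of at least one is 1 − 0.9^k.

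| k | Expected | At least one |
|---|---|---|
| 10 | 1.0 | 65 % |
| 15 | 1.5 | 79 % |
| 20 | 2.0 | 88 % |
| 25 | 2.5 | 93 % |

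A simulation of 1,500 trials (252 patients, 8 % failures, 20 noise candidates) gave a mean of 1.84 entries, at least one in 85 % of trials, and a median of about 7 failures per model term (arm plus selected variables). A second simulation, with 20 binary candidates and about 18 failures, gave a mean of 2.1.

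**Effect on inference, arm forced into the model.**
- Two-sided 5 % test of the arm: 4.3 % rejections with selection and 4.3 % without.
- SD of the treatment log odds ratio: 0.521 with noise selection against 0.506 unadjusted; 0.521 / 0.506 = 1.03.
- In the second simulation, with one truly prognostic candidate: 0.559 with screening against 0.534 with that covariate pre-specified; 0.559 / 0.534 = 1.05. Interval coverage was not materially harmed.

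**The arm under the screen, taken to the letter.** Exact enumeration over Fisher, likelihood-ratio and Wald tests, 126 per arm, control success 92 %. Probability that the arm has P ≥ 0.10:
- intervention 92 %: 89 to 94 %
- intervention 87 %: 63 to 71 %
- intervention 82 % (at the margin): 22 to 29 %

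With 140 per arm the ranges are 89 to 94 %, 60 to 68 % and 19 to 24 %.

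**The case against.** **A reader might infer that the rule removes the treatment arm.** To the letter it would, in about nine trials in ten when the arms are equal. The documents do not support this as the plan's intention: the logistic sentence says the model is there to estimate the effect of counter-referral, which requires the arm. What remains is a missing exemption, a wording defect.

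**A reader might infer that the primary analysis is affected.** The rule follows the Cox sentence and speaks of one multivariate model, and only the Cox regression is called multivariate. On that reading it governs event-free survival only, no event rate is given for it, and the count of about 20 failures does not apply. The logistic reading is also possible, since that model estimates the treatment effect too. The text does not settle it. On either reading the covariates of a randomised comparison are picked by P-value.

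**A reader might infer inflated error or a notable loss of precision.** The simulations show neither. Nor does pre-specifying a prognostic covariate shrink the standard error of a log odds ratio. A check with one binary predictor (prevalence 30 to 50 %, odds ratio 2 to 5, both assumed) gave mean standard errors of 0.482 to 0.486 unadjusted and 0.486 to 0.500 adjusted. Any gain is in power. A strong predictor would also usually pass the screen: about 94 % of trials at odds ratio 5 and 72 % at 3, but only 41 to 44 % at 2. This part of the objection stands, and it limits the point to how the model is defined.

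**An article may leave the candidate list to a fuller plan.** True, and the missing list is not the complaint. The entry rule itself is stated, and it is the rule that is poorly chosen.

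**Conclusion.** The point holds as a correctable weakness in a stated rule. Assuming 10 to 25 candidates, about 1 to 2.5 noise variables are expected in the multivariate model. If the rule reaches the primary outcome, the model rests on about 20 to 22 failures under the design rate of 92 % success. Test size and coverage are practically unaffected and the spread of the log odds ratio rises by about 3 to 5 % under the simulated conditions, so nothing here shows that a trial conclusion would change. The harm is that the adjusted odds or hazard ratio cannot be defined before the data are seen, that the rule's scope and the arm's place are unstated, and that baseline CCS class may or may not be adjusted for. The change should be made before analysis; it does not call the trial's validity into question.

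**What to change.** Replace the screening sentence with one stating that:

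- every treatment-effect model, logistic and Cox, always contains the randomised arm and baseline CCS class (I or II);
- at most a few further prognostic covariates are added, named before the data are analysed and kept whatever their P-values;
- univariate screening at P < 0.10 is confined to a separate analysis of predictors, labelled exploratory.

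This settles the scope question, guarantees the arm its place and fixes the estimand in advance. The cost is a small wording change: baseline CCS class is already collected and the sample size does not change. The one downside is that a covariate that would have passed the screen may be left out; it can still be reported in the exploratory analysis. The fix does not address how an odds ratio relates to a non-inferiority margin set on the proportion scale, which is a separate question.

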## Methods/design

### Study design

This randomized non-inferiority trial was designed to compare two groups: CAD patients meeting outpatient clinic discharge criteria, counter-referred from tertiary to primary care for follow-up with telemedicine monitoring (intervention group); and CAD patients meeting outpatient clinic discharge criteria with follow-up at the original tertiary care outpatient clinic (control group).

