### Intervention

The intervention will be discharge from the tertiary outpatient clinic and referral to the primary care facility nearest to the home address, with clinical support from an existing telemedicine platform and a toll-free hotline (TelessaúdeRS/UFRGS). Prompt access to the tertiary outpatient clinic will be ensured in acute situations following agreement between primary physicians and teleconsultants. The toll free line is accessible to primary care physicians is available Monday through Friday, from 8:00 a.m. to 5:30 p.m. [11].

A TelessaúdeRS/UFRGS team designated for the project includes one specialized cardiologist with access to the patient’s electronic record, whose role will be to aid primary care physicians in patient management, and a medical student dedicated to manage and monitor the study flowchart.

The control group will undergo the routine follow-up scheme, with appointments scheduled every six months or once yearly at the outpatient Ischemic Cardiopathy Clinic at HCPA.

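### ITT is the only analysis set named for a non-inferiority primary outcome; if intervention patients keep receiving tertiary-type care outside the agreed route, a true deficit is diluted, and no supporting analysis would show it

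*Protocol article*

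**What the plan says.** The Study design section states the aim: "This randomized non-inferiority trial was designed to compare two groups". The Study population and sample size section sets the design values, "considering a non-inferiority margin of 10 % and incidence of 92 % of the main outcome", with 140 patients per group.

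The Statistical analysis section gives one analysis set for the primary outcome: "Primary outcome analysis will be according to intention to treat (ITT". The article names no per-protocol or as-treated set.

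Three other places bear on what ITT will measure:
- **Randomization** has intervention patients discharged from the tertiary clinic and directed to a primary care unit.
- **Intervention** allows a return by agreement: "Prompt access to the tertiary outpatient clinic will be ensured in acute situations following agreement between primary physicians and teleconsultants".
- **Outcome measures and assessment procedures** lists, as a secondary outcome, "medical appointment in primary care facility taking place within not more than six months after referral". Attendance is therefore measured and not taken for granted.

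The article gives no expected rate of non-attendance or of continued tertiary care.

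**The concern.** In a superiority trial, deviations that make the two arms' care alike work against the claim. In a non-inferiority trial they work for it, because they pull the observed difference towards zero and away from the margin. ITT alone is then not reliably conservative.

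The article gives some reason to expect imperfect delivery. Its Background says that the referral and counter-referral system, on which the intervention depends, is frequently not followed, partly because primary care staff feel ill-equipped for cases that they see as complex. If that leads some discharged patients back to routine tertiary follow-up, the trial could declare non-inferiority partly because the two arms received similar care. The result would then be used to discharge stable patients more widely.

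**Working it through.** **Inputs from the article.** Control rate 92%; margin 10% (read as absolute percentage points); "a ß of 0.9 and an α of 0.05 (two-sided) were considered" (0.9 read as power); 140 per arm; 10% loss to follow-up.

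**The plan's own figure.** With equal true rates of 92% and unpooled variance, n = (z_α + z_β)² × 2 × 0.92 × 0.08 / 0.10².
- One-sided 0.05: (1.645 + 1.282)² × 0.1472 / 0.01 = 126.1, so 127. Then 127 × 1.1 = 139.7, so 140. This reproduces the stated size.
- One-sided 0.025 (two-sided 0.05 as written): (1.960 + 1.282)² × 0.1472 / 0.01 = 154.7, so 155. This becomes 171 (× 1.1) or 173 (/ 0.9), and does not reproduce.

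The stated size matches one level and the wording another, so both are carried below. Evaluable patients: 140 × 0.9 = 126 per arm.

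**Case A: crossovers do as well as controls.** Assumptions: the true rate is 82% in those treated as allocated (a deficit equal to the margin), and a fraction f of the intervention arm in fact receives tertiary-type care with a 92% rate.
- Intervention-arm rate: p_T = 0.82(1 − f) + 0.92f
- SE = √{[0.92 × 0.08 + p_T(1 − p_T)] / 126}
- P(declare non-inferiority) = Φ{[0.10 − (0.92 − p_T)] / SE − z}

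| f (assumed) | p_T | ITT deficit | SE | One-sided 0.025 | One-sided 0.05 |
|---|---|---|---|---|---|
| 0 | 0.82 | 10 points | 0.0419 | 2.5% | 5.0% |
| 10% | 0.83 | 9 points | 0.0413 | 4.3% | 8.0% |
| 20% | 0.84 | 8 points | 0.0406 | 7.1% | 12.5% |
| 30% | 0.85 | 7 points | 0.0399 | 11.3% | 18.6% |

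Example, f = 20%: 0.02 / 0.0406 = 0.492; Φ(0.492 − 1.960) = 7.1%; Φ(0.492 − 1.645) = 12.5%.

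Exact binomial enumeration of the confidence-limit rule at one-sided 0.05 gives slightly more: 5.5%, 8.7%, 13.3% and 19.6%.

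**Case B: discharged patients who never attend do the same as attenders (82%).** p_T stays at 0.82 and the rate stays at 2.5% or 5.0%. There is no dilution.

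**Case C: non-attenders do worse than attenders.** At one-sided 0.05:
- 77% in non-attenders: 3.9% (f = 10%) or 3.0% (f = 20%).
- 72% in non-attenders: 3.0% (f = 10%) or 1.8% (f = 20%).

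ITT is conservative here.

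**What a per-protocol set would cost in power.** With equal true rates of 92%, power = Φ{0.10 / √(2 × 0.92 × 0.08 / m) − z}, where m is the number per arm. If 10% or 20% of both arms are excluded (assumed), 126 falls to about 113 or 101. Power is then 79% or 74% at one-sided 0.025, and 87% or 83% at one-sided 0.05. With all 126 it is 83% and 90%.

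**The case against.** The strongest reply is that ITT fits the question. The article sets out to estimate the effect of a counter-referral strategy, and failing to obtain a primary care appointment is one consequence of that strategy. ITT counts that consequence. This stands, and it is why ITT should remain primary.

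A reader might infer that any patient who never takes up primary care dilutes the deficit. The article does not support that. Such a patient has been discharged from the tertiary clinic and does not by default receive control care. Cases B and C show that ITT may then be neutral or conservative. It can be argued that a stable non-attender who merely continues existing prescriptions might resemble a control seen once a year, but this is conjecture and the article gives no data on it.

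Return to tertiary care by joint agreement is part of the strategy under test, so it is not contamination. What remains is unplanned crossover. It is possible, but the article neither reports nor predicts a rate.

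A per-protocol set can also mislead. Suppose attenders reach 85%, 20% of the arm never attend and reach 72%, and controls reach 92% (all assumed). The ITT rate is 0.8 × 0.85 + 0.2 × 0.72 = 0.824, a deficit of 9.6 points. Dropping non-attenders leaves a deficit of 7 points, which looks safer than ITT. This objection stands and shapes the fix.

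Finally, the full protocol or analysis plan, not shown here, may name further sets. If it does, confirming that is enough.

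**Conclusion.** The point holds in a limited, conditional form. Naming ITT alone leaves the non-inferiority claim unprotected against one specific deviation: intervention patients who continue tertiary-type care without agreed re-referral. If 10% to 30% did so and fared as well as controls, the chance of wrongly declaring non-inferiority at a true 10-point deficit would be 4.3% to 11.3% against a nominal 2.5%, or 8.0% to 18.6% against 5.0%.

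These figures rest on the assumed crossover range, an absolute margin, a 92% control rate and 126 evaluable per arm. They do not show that ITT is the wrong primary analysis, nor that non-attendance alone inflates the error. A pre-specified supporting analysis is warranted; a change of primary analysis is not.

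**What to change.** Keep ITT as the primary analysis. Pre-specify a supporting per-protocol analysis of the primary outcome, using the same risk difference, confidence interval and −10-point margin as the ITT comparison.

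- **Main version.** Define a deviation mainly as receiving the other arm's care: intervention patients who continue routine tertiary follow-up without agreed re-referral, and controls who are moved to primary care. Agreed re-referral is not a deviation.
- **Second version.** Also require the primary care appointment within six months. Show the outcomes of non-attenders separately, because dropping them can favour the intervention.
- **Interpretation.** Read the analyses together. Report any per-protocol confidence limit beyond the margin as weakening the non-inferiority claim.

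**Cost.** The sample size does not change. The supporting set is not fully randomised and is smaller, with power of about 74–79% (one-sided 0.025) or 83–87% (one-sided 0.05) if 10–20% are excluded from both arms. The six-month appointment is already an outcome, but the article does not list crossover visits as recorded data. They must be taken from clinic records or asked about at the scheduled interviews.
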